### 4.5. Study Scheme

#### 4.5.1. Module I

**Initial Visit: Prehabilitation—Patient Admission and Initial Assessment (21 +/− 7 days before surgery)**

The initial visit includes presenting the potential participant with verbal and written information about the proposed study, providing a copy of the “Information for Study Participants” document, and providing a copy of a written informed consent form for participation in the study. At this stage, the participant should be fully informed by the Investigator about the study’s nature and schedule and their rights and responsibilities and receive detailed information from the Investigator on all relevant aspects, including the potential risks and benefits of participation.

Because eligibility can be confirmed without additional diagnostic testing solely for research purposes, the initial eligibility assessment may be combined with Visit 1. Participants who need additional time to review the informed consent form and participant information document may complete consent at a subsequent visit before any study-specific procedure is performed.

Every participant will be informed of their right to withdraw from the study at any stage without the need to provide a reason. Before any study procedure is initiated, the process of obtaining informed consent from the participant must be fully completed.**Visit 1: Following Completion of Informed Consent Process**

1. The participant’s completion of the informed consent procedure will be documented, and the randomization process (Principal Investigator, Investigator) will be completed.

2. The Investigator will confirm in writing that the participant meets the inclusion/exclusion criteria on the designated study form.

3. Demographic and medical history interviews: The participant will respond to questions according to the study questionnaire, covering topics such as lifestyle habits, family history of cancer, and level of independence.

4. The American Society of Anesthesiologists (ASA) classification will be used to evaluate surgical risk related to serious complications or mortality during or after anesthesia.

5. A quality-of-life assessment using the SF-36 questionnaire will be provided to the patient, enabling them to self-evaluate their health status.

6. Pain intensity will be determined via the Numeric Rating Scale (NRS).

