7. Physical functioning will be assessed via the Zubrod–ECOG–WHO scale (Eastern Cooperative Oncology Group), which is commonly used to evaluate the general condition and quality of life of cancer patients and in geriatrics, psychiatry, and chronic diseases.

8. The Charlson Comorbidity Index (CCI) will be used to estimate the 10-year survival probability in patients with multiple comorbidities.

9. Venous thromboembolism risk will be evaluated using the Caprini scale.

10. An assessment using the G8 scale for geriatric screening will be performed.

11. For older adults, a health status assessment will be conducted using the Vulnerable Elders Survey (VES).

12. The participant’s need for specialist consultations will be assessed (coordinated under SOSNP).

13. Blood will be collected for laboratory testing (CBC, electrolytes, albumin, cholesterol, total protein, triglycerides, TSH, FT3, FT4, iron, vitamin D3, AST, ALT, and GGTP) and biobanking. At the 4th Military Clinical Hospital, the protocol-defined allostatic load panel will additionally be assessed.

14. A nutritional assessment, including anthropometric measurements (BMI, WHR), a nutritional status evaluation using bioelectrical impedance analysis (BIA), and a clinical dietitian interview will be conducted.

15. A psychological evaluation will be conducted (HADS, MMSE).

16. Physiotherapy assessment: Grip strength (dynamometer), a six-minute walk test (6MWT), a FEV-1 test, and a sit-to-stand test (using a wristband) will be conducted.

17. A participant activity assessment will be conducted using a smart wristband. A mobile app will be installed on the participant’s smartphone that will store and cycle data from the wristband, such as step count, sleep duration, and heart rate. Training will be provided on wristband usage, measurement techniques, app functionality, and technical support.

18. Clinical pharmacist assessment: A medication review will be conducted.

19. Addiction-related re-education will be conducted (if applicable).

The collected data will serve as a baseline for evaluating study endpoints (initial assessments).**Visit 2: Summary Prehabilitation Visit (Hospital Admission Day For Surgery)**

1. Health Status Update: A targeted interview will be conducted to assess any changes in the participant’s general health status since the first visit. A visit form will be completed, and scales will be reassessed for comparison with Visit 1 results.

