### 5.1. Primary Endpoints

Participants with prolonged index hospitalization.

The outcome will be reported as the number and percentage of participants whose index hospitalization lasts at least 14 calendar days. The number of days beyond day 14 and the number of consecutive clinically unjustified Red days at the end of hospitalization will also be recorded.

2.Participants with an unplanned hospital readmission within 30 days after index hospital discharge.

Readmissions will be identified using electronic health records, hospital information systems, and participant follow-up interviews. The outcome will be reported as the number and percentage of participants with at least one unplanned readmission within 30 days after discharge.

Prolonged hospitalization and readmission will be compared between the RESET and standard-care arms. Additional analyses will describe the duration and reasons for prolonged hospitalization, time to readmission, causes of readmission, associated treatment, impact on the participant’s condition, and related costs.

3.Participants with at least one postoperative complication within 30 days after surgery.

Postoperative complications will be identified and graded using the Clavien–Dindo classification. The outcome will be reported as the number and percentage of participants with at least one Clavien–Dindo grade I-V complication within 30 days after surgery. For participants with multiple complications, the highest grade observed during this period will additionally be recorded.

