Exploratory comparisons with eligible non-participants will be kept separate from the randomized analyses. Because RESET includes clinically heterogeneous operations and specialty-specific risk profiles, a single propensity-score model would not be appropriate across all surgical populations. Where propensity-score methods are used, the model will be defined prospectively within clinically coherent groups before outcomes are compared. Adjustment will be limited to characteristics recorded before the decision to participate and available in a comparable form for both participants and non-participants. The covariate set will be selected from routinely available demographic, center, calendar-period, and procedural characteristics, with additional specialty- or procedure-specific baseline factors included when clinically relevant and consistently available. Variables arising after study participation will not be used. Covariate balance and overlap between groups will be checked before adjusted comparisons are interpreted. These analyses will remain exploratory and will not influence the primary randomized treatment-effect analyses. For transparency, the prespecified core covariate set for any propensity-score analysis will comprise age, sex, study site, calendar year, ASA physical status class, Charlson Comorbidity Index, and broad surgical-procedure category. Propensity-score analyses will be undertaken only within clinically coherent groups in which these core variables are recorded before the decision to participate and are available in a comparable form for participants and eligible non-participants. Any additional specialty- or procedure-specific baseline covariate must be clinically justified and defined before outcome comparison and must be consistently available in both groups.

Analyses of accumulated data may be conducted annually to support implementation monitoring and prespecified interim publications. Final analyses will be performed after completion of follow-up. Study year and site may be included as covariates to evaluate temporal and center-related variation; these analyses will not replace the prespecified randomized comparison.

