### 5.9. Ethical Approval

The study is conducted in accordance with the Declaration of Helsinki, applicable Polish regulations, Good Clinical Practice principles, and the approved protocol. Ethical approval was granted by the Bioethics Committee at the Lower Silesian Medical Chamber in Wroclaw (approval No. 33/BNBO/2025, 12 November 2025). Important protocol modifications will be submitted to the Bioethics Committee, incorporated into study documentation, and reflected in the public registry and subsequent publications when applicable.

In addition to the randomized cohort, the approved study framework permits exploratory analyses of routinely collected clinical outcomes among otherwise eligible patients who decline participation. These patients are not enrolled in RESET, undergo no study-specific procedures, and receive no study-specific intervention. The non-participant component is therefore a secondary record-based analysis of existing clinical data. Under Chapter 4 of the Polish Act of 5 December 1996 on the Professions of Physician and Dentist (consolidated text: Journal of Laws of 2026, item 37, as amended) [45], Article 21 defines medical experiments conducted on humans and Article 29 requires a positive opinion on a medical-experiment project from an independent bioethics committee. Because this component involves no study-specific intervention, patient contact, or collection or analysis of biological material for research, it does not meet the statutory definition of a medical experiment. Accordingly, a separate positive bioethics-committee opinion under Article 29 and study-specific research consent are not required under the cited provisions. The analysis will be conducted in accordance with the Declaration of Helsinki and applicable data-protection requirements. These non-participant analyses will remain exploratory and will not contribute to the primary randomized treatment-effect estimates.

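### In the exploratory non-participant comparison, readmission and complications are sought more thoroughly in participants than in decliners, and no pre-decision source is named for the compulsory ASA and Charlson scores.

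*Protocol article*

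**What the plan says.** Section 5.3 sets up a secondary track that may compare four outcomes with eligible patients who declined: prolonged hospitalization, readmission, length of stay and postoperative complications.

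**Outcomes.** Section 5 counts unplanned readmissions to any hospital, not only the index one. Section 5.1 gives the sources: "Readmissions will be identified using electronic health records, hospital information systems, and participant follow-up interviews". It also counts any Clavien–Dindo grade from I to V within 30 days. Module III (Section 4.5.3) schedules Clavien–Dindo classification, and the follow-up visit at day 30 ± 5 includes an interview that documents the postoperative course. For decliners, Section 5.9 states: "These patients are not enrolled in RESET, undergo no study-specific procedures, and receive no study-specific intervention". It describes their component as an analysis of existing records without patient contact.

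**Covariates.** Section 5.3 sets a general rule: "Adjustment will be limited to characteristics recorded before the decision to participate and available in a comparable form for both participants and non-participants". It then states that "the prespecified core covariate set for any propensity-score analysis will comprise age, sex, study site, calendar year, ASA physical status class, Charlson Comorbidity Index", together with broad procedure category, and adds the condition "Propensity-score analyses will be undertaken only within clinically coherent groups in which these core variables are recorded before the decision to participate". In the study schedule both scores appear under Visit 1, which follows consent: "The American Society of Anesthesiologists (ASA) classification will be used to evaluate surgical risk" (item 4) and "The Charlson Comorbidity Index (CCI) will be used to estimate the 10-year survival probability" (item 8). Randomization is item 1 of the same visit.

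**Limitations.** The Discussion warns of residual selection bias in this comparison. It does not mention differences in how outcomes are found.

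**The concern.** An event that can be found in one group and not in the other produces a difference even when the true risks are equal. Two of the four outcomes in this track are open to that. An admission elsewhere that a participant reports at interview, or a minor complication that comes to light only at the day-30 contact, counts for a participant. The same event in a decliner may leave no trace in the hospital's records.

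Propensity scores cannot repair this, and balance checks cannot show it, because both work on baseline covariates. The comparable-form rule in Section 5.3 is likewise confined to covariates.

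Precision adds to the risk. Decliners are expected to outnumber randomized controls several times over, so the less reliable comparison will carry the narrower interval. Section 5.3 also foresees interim publications while recruitment is under way.

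The covariate side is a smaller matter. Two scores are made compulsory and must predate the participation decision, but the article describes their recording only after that decision.

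**Working it through.** **Step 1. Group sizes.** The article screens 12,800 patients and assumes 30% decline (Section 4.2). 12,800 × (1 − 0.30) = 8960, which reproduces the stated randomized total. The complement is 12,800 × 0.30 = 3840 decliners (3200 to 4480 at the stated 25–35%). By population, at 30%:
- oncology: 5740 / 0.70 × 0.30 = 2460
- non-oncology: 3220 / 0.70 × 0.30 = 1380

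**Step 2. Sources side by side.**

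| Outcome | Participants | Decliners | Exposed? |
|---|---|---|---|
| Readmission | Records plus interview, any hospital | Existing records | Yes |
| Complications, grades I–V | Scheduled grading plus day-30 interview | Existing records | Yes |
| Prolonged hospitalization | Admission and discharge dates | Same | No |
| Length of stay | Admission and discharge dates | Same | No |

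**Step 3. Size of the artefact.** Let p be the true risk, equal in both groups, and m the share of patients with the outcome whose only qualifying event is found through study follow-up. Participants show p and decliners show p(1 − m), so the spurious difference is p × m. The article gives no value for m; the ranges are assumptions. The values of p are the planning control risks in Table 2.

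| Outcome | p | Assumed m | Decliners show | Artefact p × m |
|---|---|---|---|---|
| Complications, oncology | 30% | 10–30% | 27–21% | 3.0–9.0 points |
| Complications, non-oncology | 25% | 10–30% | 22.5–17.5% | 2.5–7.5 points |
| Readmission, oncology | 12% | 10–25% | 10.8–9.0% | 1.2–3.0 points |
| Readmission, non-oncology | 10% | 10–25% | 9.0–7.5% | 1.0–2.5 points |

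The participants' figure is always the higher one, so the artefact works against RESET.

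**Step 4. Would it be noticed as chance?** For oncology readmission, compare 5170 RESET patients with 2460 decliners, using the normal approximation for two proportions with pooled variance under the null and a nominal two-sided 0.05. With no true difference, the probability of a significant result against RESET is about 11% at m = 5%, 33% at 10% and 88% at 20%.

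The standard error at 12% risk is √(0.12 × 0.88 × (1/5170 + 1/2460)) ≈ 0.8 points against decliners. Against the 570 randomized controls it is √(0.12 × 0.88 × (1/5170 + 1/570)) ≈ 1.4 points.

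**Step 5. Covariates.** No arithmetic applies. Visit 1 values come after consent, so they fail the timing rule, and decliners have no Visit 1. Section 5.3 first says that "The covariate set will be selected from routinely available demographic, center, calendar-period, and procedural characteristics", with specialty-specific additions; ASA and Charlson are not on that general list, yet both then become compulsory. The routine outpatient visit described in Section 4.3 takes a comorbidity history but names neither score, and patients may join the waiting list without attending in person. No qualifying source is therefore named, although none is excluded.

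**The case against.** The case on the other side is substantial.

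- **The covariate rule is a gate.** Propensity scores are to be used only where the condition is met, and Section 5.3 bars variables arising after participation. A reader might infer that the comparison cannot be run at all, or that Visit 1 scores will be used regardless. The documents support neither. Routine data from before the offer may exist, and if they do not, the propensity-score analysis is simply not done. Nor does the article support the idea that comorbidity would be scored higher in participants. What stands is narrower: two compulsory scores have no named source that meets the rule.
- **The article leans towards record-only outcomes.** It calls the compared outcomes routinely available and the decliner component record-based. The interview source belongs to the primary endpoint definition, whose stated comparison is between the randomized arms. This partly answers the point. But the record-based description concerns the decliners, and nothing limits participants to record-found events. The only operational definitions of these two outcomes include follow-up sources.
- **The size is assumed.** This is correct. The top of the oncology complication range happens to equal the 9.0 points in Table 2, but that figure is a detectable difference for the randomized comparison and is not a yardstick for this track.
- **The track is optional, exploratory and separate.** This is also correct, and the artefact alone could not create a false claim of benefit. It could hide a benefit or suggest harm.

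**Conclusion.** The point holds for readmission and postoperative complications in the exploratory non-participant track. If participants' outcomes there follow the definitions in Sections 5 and 5.1, the comparison is biased against RESET, and neither the covariate rule nor the stated limitation covers it.

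The magnitude is not known. The illustrative 3–9 points (oncology complications) and 1.2–3.0 points (oncology readmission) rest on three assumptions: equal true risks, the Table 2 planning risks, and an assumed share of outcomes found only through follow-up.

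The covariate part is a matter of specification: the sources for ASA and Charlson need to be named. It does not show that the analysis is impossible or that prohibited values will be used. Prolonged hospitalization, length of stay and all randomized analyses are outside this point.

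**What to change.** For the non-participant track only:

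1. State that readmissions and complications count in both groups solely when found in record sources available for both. Record a source flag on each participant event so that events found only through study follow-up can be set aside. The flag is easiest to collect prospectively, and recruitment is already under way.
2. Add differential outcome ascertainment to the stated limitations, beside selection bias.
3. Derive the Charlson index in both groups from routine diagnoses dated before the participation offer, not from Visit 1.
4. Keep ASA in the core set only where a routine value from before the offer exists in both groups. Otherwise run the propensity-score analysis without it and say so.

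The cost is wording in the protocol and SAP plus one data field. Fewer events will be counted in this track, and where ASA is dropped some confounding by anaesthetic risk may remain. A minimum complication grade is not needed for the repair; it would be a matter of preference. The randomized analyses do not change.

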### 5.4. Sample Size

The approved protocol specifies a two-sided significance level of α = 0.01 and a target statistical power of 95% for the primary analyses. The recruitment target itself, however, was constrained primarily by feasible surgical volumes rather than obtained by solving a single power equation. Based on 2023 surgical volumes and anticipated pre-randomization non-participation, approximately 5740 oncological participants (about 570 control and 5170 RESET) and 3220 non-oncological participants aged ≥70 years (about 320 control and 2900 RESET) are expected to be randomized, for an overall randomized sample of approximately 8960.

The approved protocol also reported reference calculations for selected statistical models. For logistic regression of prolonged hospitalization/readmission, an odds-ratio magnitude of 1.30, Pr(Y = 1 | X = 1) under H0 = 0.20, two-sided α = 0.01, and 95% power yielded *N* = 1632 in G*Power version 3.1.9.7 [42]. A repeated-measures MANOVA reference calculation for multidomain health-status outcomes (Pillai’s V = 0.01) yielded *N* = 1721. The protocol did not contain three independently derived endpoint-specific calculations, nor a separate original event-rate assumption or power calculation for postoperative complications.

To provide the endpoint-specific justification requested by the Reviewer and to characterize the fixed design transparently, Table 2 additionally reports current prospective operating-characteristic benchmarks for each primary outcome and clinical population. These calculations do not alter the approved recruitment target or reconstruct the original protocol calculation. They use the planned 9:1 group sizes, 95% power, and the most stringent first-step Holm threshold for the six-test family (two-sided α = 0.01/6 = 0.00167). Plausible control-event-rate scenarios were selected by the Investigators from participating-center historical experience and the literature considered during trial planning. The calculations use the normal approximation for two independent proportions without continuity correction.

Because Holm’s procedure is step-down, α = 0.00167 is a conservative single-hypothesis benchmark rather than the threshold applied to every ordered test. The detectable effects in Table 2 should therefore be interpreted as worst-step design-sensitivity benchmarks; the full family-wise operating characteristics depend on the joint pattern of the six primary *p* values. The SAP, finalized before database lock and before treatment effects are examined, will document these assumptions and may supplement them with simulation-based scenarios using blinded pooled event-frequency information. This prospective characterization will not alter the recruitment target, allocation ratio, endpoints, or protocol-defined α and power targets.

The protocol did not provide a detailed narrative rationale for the α = 0.01 and 95% power combination, so the original specification is distinguished here from the explanatory rationale added in this revision. Retaining a stringent α reduces the risk that isolated primary findings are over-interpreted in a trial with multiple primary comparisons and an extensive secondary and implementation program, while the 95% power target reflects a preference for stronger assurance that clinically meaningful effects are not missed. With the fixed, large recruitment base, this conservatism translates into a larger minimum detectable effect rather than a larger recruitment target: for prolonged hospitalization in the oncology population, the detectable absolute reduction is approximately 4.6 percentage points under α = 0.05 with 80% power, 6.8 percentage points under α = 0.01 with 95% power, and 7.6 percentage points using the conservative first Holm step at α = 0.00167 with 95% power. The Investigators considered this evidential standard appropriate because RESET is intended to inform system-level implementation and potentially reimbursement, where false-positive conclusions would have substantial organizational and financial consequences.

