## 2. Materials and Methods

### 2.1. Study Design

This is a prospective, two-center, two-arm, parallel-group randomized controlled study evaluating the RESET perioperative care pathway in two predefined surgical populations. Participants who provide written informed consent and meet the eligibility criteria are randomized in a 9:1 ratio to the RESET intervention or standard-care control arm. Exploratory analyses may additionally use routinely collected clinical outcomes from a naturally formed group of eligible patients who do not participate, as prespecified in the approved protocol. The study was approved by the Bioethics Committee at the Lower Silesian Medical Chamber in Wroclaw (approval No. 33/BNBO/2025, 12 November 2025). Protocol version 1.2, dated 27 March 2026, was developed in accordance with the SPIRIT 2013 Statement (Additional File 1) [33]. The study is being conducted at the Regional Specialist Hospital in Wroclaw and the 4th Military Clinical Hospital with Polyclinic in Wroclaw.

The primary treatment effect of interest is the effect of assignment to the RESET pathway, compared with standard perioperative care, on each of the three primary outcomes: postoperative complications, prolonged index hospitalization, and 30-day unplanned hospital readmission. Each outcome will be evaluated separately within the oncology and non-oncology populations, yielding six primary hypothesis tests. Primary analyses will follow the intention-to-treat principle, with per-protocol analyses used as supportive assessments. The confirmatory decision rule and multiplicity control across all six outcome-by-population tests are specified in the Statistical Methods section of this paper. The overall study design and participant flow are presented in Figure 1.

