#### 4.2.1. Randomization

After written informed consent and confirmation of eligibility, each participant is assigned a unique study identification number. Randomization is performed centrally through a secure web-based system using a computer-generated dynamic allocation procedure based on a biased-coin algorithm. The procedure monitors cumulative allocation within each predefined clinical population and adjusts assignment probabilities as needed to maintain the protocol-defined 9:1 intervention-to-control ratio. Allocation is generated only after participant enrollment and eligibility confirmation and cannot be predicted or modified by Recruiting Investigators.

The unequal 9:1 allocation was chosen a priori for ethical and implementation reasons, principally to allow the greatest possible proportion of seriously ill surgical patients—particularly those undergoing oncological surgery—to receive the low-risk, multimodal RESET pathway while retaining a randomized standard-care comparator. The lower statistical efficiency associated with the smaller control group was taken into account in the approved sample-size planning described below. Under the simplifying assumption of equal outcome variances and a fixed total sample size, a 9:1 allocation has approximately 36% of the statistical efficiency of a 1:1 allocation for a simple two-group contrast (approximately 2.78-fold higher variance and 1.67-fold higher standard error). The substantially larger total recruitment target and prespecified covariate-adjusted analyses improve precision but do not eliminate this intrinsic efficiency penalty.

Randomization is conducted separately within the oncology and non-oncology populations. Allocation data are kept separate from participant-identifying and outcome data. No fixed block sizes or additional stratification factors are used beyond the separation of the two predefined clinical populations.

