## 6. Discussion

RESET evaluates an integrated perioperative pathway combining individualized prehabilitation, coordinated inpatient care, structured discharge planning, and transitional care. Existing evidence suggests that prehabilitation can improve functional capacity and selected postoperative outcomes, but effects vary across populations, intervention content, and implementation settings [1,4,6,7,8,9,10,11,12,13,14,15,16]. The present trial therefore tests the effectiveness of the integrated pathway rather than assuming that benefits of individual elements will translate directly to the complete RESET model.

The clinical rationale is particularly relevant to patients with cancer and older surgical patients, in whom limited physiological reserve, frailty, multimorbidity, nutritional deficits, and short preoperative windows may modify response to optimization. Prolonged hospitalization and readmission are also multifactorial outcomes that reflect perioperative morbidity, discharge preparation, access to follow-up, patient and caregiver support, and organizational factors [29,30,31]. RESET addresses these domains within one coordinated pathway spanning the preoperative, inpatient, and 30-day post-discharge periods.

The 9:1 allocation increases experience with delivery and implementation of RESET while preserving a randomized standard-care comparator, but the smaller control group necessarily reduces statistical efficiency compared with balanced allocation. The protocol’s generic reference calculations should therefore not be interpreted as guaranteeing 95% power for every endpoint-population hypothesis. The current manuscript reports conservative endpoint-specific design-sensitivity benchmarks under the planned allocation and the first Holm step; the SAP will document the full family-wise operating characteristics before database lock and before treatment effects are examined.

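### The reference figure N = 1632 fits a standard-normal continuous predictor, not a two-arm comparison, and the article attributes the shortfall to the 9:1 allocation alone

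*Protocol article*

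**What the plan says.** Section 5.4 of the protocol article gives the design targets: "The approved protocol specifies a two-sided significance level of α = 0.01 and a target statistical power of 95% for the primary analyses". It then says that feasible surgical volumes, rather than one power equation, mainly fixed the recruitment target, and it lists the planned groups: "approximately 5740 oncological participants (about 570 control and 5170 RESET) and 3220 non-oncological participants aged ≥70 years (about 320 control and 2900 RESET").

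Next comes older material: "The approved protocol also reported reference calculations for selected statistical models". One of these reads "For logistic regression of prolonged hospitalization/readmission, an odds-ratio magnitude of 1.30", with Pr(Y = 1 | X = 1) "under H0 = 0.20, two-sided α = 0.01, and 95% power yielded" N = 1632. Neither the distribution of X nor an allocation ratio is given. The section adds that there were no three separate endpoint calculations and none for complications. Table 2, added in revision, uses the 9:1 group sizes and the first Holm step (α = 0.01/6 = 0.00167). It shows detectable odds ratios from 0.33 to 0.62.

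Two other places bear on the figure. Section 4.2.1: "The lower statistical efficiency associated with the smaller control group was taken into account in the approved sample-size planning described below". The Discussion, directly after noting the efficiency cost of the smaller control arm, says that the protocol's "generic reference calculations should therefore not be interpreted as guaranteeing 95% power for every endpoint-population hypothesis".

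**The concern.** Participants "are randomized in a 9:1 ratio to the RESET intervention or standard-care control arm", so the predictor in the primary logistic models is binary and unbalanced. For such a predictor, 1632 is far too small at an odds ratio of 1.30. The notation Pr(Y = 1 | X = 1) invites the reader to take X as the arm indicator, and the calculation is attached to two of the three primary outcomes.

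The explanation offered also matters. Section 4.2.1 puts the variance penalty of 9:1 at 2.78-fold. A reader who accepts that allocation is the only problem would compute 1632 × 2.78 ≈ 4,540, compare it with 5,740 oncology participants, and conclude that this population is adequately powered at an odds ratio of 1.30. As shown below, it is not.

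**Working it through.** **Inputs.** From section 5.4: odds ratio 1.30 (β = ln 1.30 = 0.2624, β² = 0.06884), base probability 0.20, two-sided α = 0.01 (z = 2.576), power 95% (z = 1.645), groups 570/5170 and 320/2900. Control risks are from Table 2. In the direction of benefit the odds ratio is 1/1.30 = 0.769. A 20% control risk then gives odds 0.25/1.30 = 0.1923, a RESET risk of 16.1%.

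**1. Reproducing 1632.** For logistic regression on a predictor X, N ≈ (z₁ + z₂)² / [p(1 − p) · Var(X) · β²].

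- X standard normal, Var(X) = 1: 17.814 / (0.16 × 0.06884) ≈ 1,617.
- Wald calculation from the information matrix, same X: 1,652 without a null-variance correction; 1,619 or 1,631 with one, depending on how the null intercept is set.

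The reported 1632 lies inside this range, one away from 1,631.

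**2. A binary X.** The variance of an arm indicator is π(1 − π), at most 0.25.

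- 1:1: 1,617 / 0.25 ≈ 6,470.
- 9:1: 1,617 / 0.09 ≈ 17,970.

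The two-proportion formula (pooled null variance) gives, at 1:1, 7,032 for 20% versus 16.1% and 6,008 for 20% versus 24.5%. At 9:1 it gives about 19,200 and 16,900. Across both directions of the odds ratio, both placements of the 0.20 and the usual approximations, the range is about 6,000 to 7,100 at 1:1 and 15,800 to 20,900 at 9:1. Some variance-corrected variants widen this to 5,760–7,420 and 15,600–21,100. The smallest binary result is still 5,760/1632 ≈ 3.5 times the printed figure.

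**3. Splitting the gap.** Predictor type contributes 1/0.25 = 4-fold. Allocation contributes 0.25/0.09 = 2.78-fold, which is the article's own penalty. Together they give 11.1-fold. Allocation is the smaller part.

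**4. Power of 1632 for 20% versus 16.1%, α = 0.01.** Power = Φ[(|p₀ − p₁| − z·s₀)/s₁], where s₀ is the pooled and s₁ the unpooled standard error.

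- 816/816: (0.0387 − 2.576 × 0.01905)/0.01902 = −0.545, power 29%.
- 163/1469: (0.0387 − 2.576 × 0.03066)/0.03277 = −1.229, power 11%.

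**5. Power of the planned groups at odds ratio 1/1.30, same formula, Table 2 control risks.**

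| Population | Outcome | Control → RESET | α = 0.01 | α = 0.00167 |
|---|---|---|---|---|
| Oncology | Prolonged stay | 20% → 16.1% | 42% | 23% |
| Oncology | Readmission | 12% → 9.5% | 27% | 13% |
| Non-oncology | Prolonged stay | 15% → 12.0% | 18% | 7% |
| Non-oncology | Readmission | 10% → 7.9% | 13% | 5% |
| Oncology | Complications (outside the calculation) | 30% → 24.8% | 55% | 34% |
| Non-oncology | Complications (outside the calculation) | 25% → 20.4% | 27% | 12% |

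For prolonged stay and readmission, a Wald test on the log odds ratio agrees within about two percentage points.

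**6. Table 2.** The pooled formula at α = 0.00167 and 95% power returns detectable risks of 12.4–12.5%, 6.2%, 21.0%, 6.7%, 3.5% and 14.2%, which match the table. The 4.6, 6.8 and 7.6 percentage-point series in section 5.4 also reproduces.

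**The case against.** The strongest reply is that nothing in the design rests on 1632. The article says surgical volumes set recruitment, calls the figure one of several reference calculations, admits that endpoint-specific calculations were lacking, and disclaims a guarantee of 95% power. Table 2 shows detectable odds ratios of 0.33 to 0.62, all further from 1 than 0.77, so an attentive reader can see that 0.77 is beyond the design's 95% reach. All of this stands, and it limits the point to a wrong reference figure and a wrong explanation.

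Three stronger readings are therefore not supported:

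- A reader might infer that the article claims 95% power at an odds ratio of 1.30 under 9:1. It does not; 95% is a target, and the Discussion qualifies it.
- A reader might quote 13% to 55% as the power at the calculation's own odds ratio. The 55% belongs to oncology complications, which the calculation did not cover. For the outcomes it names, the range is 13% to 42%.
- A reader might infer that the approved planning ignored 9:1. The full approved protocol is not shown, and planning is a wider term than one calculation. Section 4.2.1 also quantifies the penalty and says that larger recruitment and covariate adjustment do not remove it.

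Nor does the plan invite reading a missed test as proof of no benefit: such results are labelled non-confirmatory, and all six are reported with confidence intervals. It is also fair that no section names 1.30 as the smallest important effect. Power at that value is worth stating only because the article itself pairs it with 95%.

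What the reply does not remove is that no section says 1632 is for a continuous predictor, and the only cause given for the shortfall is allocation.

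**Conclusion.** The concern holds as a wrong reference figure with an incomplete explanation. N = 1632 is not a sample size for RESET versus control: it is too small by at least about 3.5-fold at 1:1 and roughly 10- to 13-fold at 9:1 (15,800/1632 ≈ 9.7; 20,900/1632 ≈ 12.8). Because it fails at 1:1, allocation alone cannot account for the gap. The statement in section 4.2.1 that the approved planning took 9:1 into account finds no support in the calculation that section 5.4 reports; from what is shown, only the Table 2 benchmarks use 9:1.

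This rests on two assumptions. The standard-normal predictor is inferred from the arithmetic, not stated, though no binary split tried comes near 1632. The power figures use Table 2's planning risks and an unadjusted comparison. At the calculation's own 20% risk, power at α = 0.01 is 42% in oncology and 23% in non-oncology. The operative benchmarks in Table 2 are unaffected.

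**What to change.** 1. In section 5.4, withdraw N = 1632 as a reference for the arm comparison, or label it as applying to a standard-normal continuous covariate with the odds ratio per standard deviation.
2. State the power of the planned groups at an odds ratio of 1/1.30 for the two outcomes that calculation names, at α = 0.01 and, in brackets, at the first Holm step: oncology prolonged stay 42% (23%) and readmission 27% (13%); non-oncology prolonged stay 18% (7%) and readmission 13% (5%). If complications are added, give 55% (34%) and 27% (12%) and note that they lie outside that calculation.
3. Reconcile sections 4.2.1, 5.4 and 6 on whether and where the 9:1 ratio was accounted for. In the Discussion, give predictor type as a cause of the shortfall alongside allocation.

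The cost is a few sentences, or one extra column in Table 2. Recruitment, allocation, endpoints and α stay as they are. The downside is a less favourable stated power.
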